#### Process evaluation

A process evaluation will be used to evaluate how the intervention was implemented and to understand which factors contributed to the results of the trial. This process evaluation follows the RE-AIM framework, which highlights essential factors to improving the adoption and implementation of evidence-based interventions: Reach, Efficacy, Adoption, Implementation, and Maintenance [20]. The process evaluation will span the duration of the intervention, as well as pre and post-intervention evaluation. An overview of the process evaluation, with RE-AIM domains and data collection methods, can be found in Table 3.

### Participant timeline

The participant timeline flow diagram is represented in Fig. 1. All GPs, patients, and SDMs from the intervention and control group will complete a baseline assessment (T0) after providing informed consent. At 3 months (T1), the RA will approach the patient and SDM for follow-up assessment; GPs will complete a follow-up assessment by filling out and returning questionnaires by postal mail or by completing an online version of the questionnaire. Six months (T2) after inclusion, patients and SDMs will complete the second follow-up by filling out and returning questionnaires by postal mail; GPs will also complete follow-up measures at this time by filling out and returning questionnaires by postal mail or by completing an online version of the questionnaires.

**Fig. 1 Fig1:**
[figure not shown]
Flow diagram of the ACP-GP trial

### Sample size

All power calculations were conducted to allow testing for intervention effectiveness at T1. Power calculations were conducted for the primary outcome at the patient level and at the GP level.

When all clusters have the same size of 2 patients, and we assume an intracluster correlation coefficient (ICC) of 0.04 [32], then the design effect is estimated at 1.04, and a sample of 26 patients for each group (corresponding to 13 GPs with each 2 patients) will achieve 91.45% power to detect a mean difference in delta outcome of 1 at a significance level of 2.5%, assuming the standard deviation is 0.96 in both groups. This number has been increased to 51 patients per group (corresponding to 17 GPs with each 3 patients) to allow for an initial GP drop-out rate of 23.53% and a patient drop-out rate of 33.33%. (Total sample size of 102 patients).

A sample of 14 GPs for each group will achieve 91.11% power to detect a mean difference in ACP self-efficacy of 1 at a significance level of 2.5%, assuming the standard deviation is 0.71 in both groups. This number has been increased to 18 GPs per group to allow for an initial GP drop-out rate of 22.22% (Total sample size of 36 GPs).

To ensure sufficient statistical power for both GP- and patient-level primary outcomes, we will use the more conservative calculation of 18 GPs per group (36 total), with 54 patients per group (108 total) and a maximum of 54 SDMs per group (1 per patient, 108 total).

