#### Data analysis

The intent-to-treat population consists of all patients randomized. Subjects are analyzed according to the allocated treatment group irrespective of their compliance with the planned course of treatment. The intent-to-treat population is considered the main analysis population.

Linear mixed models will give unbiased results when outcome data is missing at random (maximum likelihood estimation). GEE models only allow for missing values to be completely at random (it is not a likelihood approach).

The analyses of the two separate primary endpoints will be performed at the two-sided 2.5% significance level, because success on any one of these endpoints at T1 may support a conclusion of effectiveness (Bonferroni method to adjust for multiplicity).

When an effect on a primary endpoint is shown, the secondary endpoints can be analyzed at the two-sided 5% significance level.

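### The two powers printed in the sample size section are slightly too high for the numbers they are attached to; a minor reporting correction that changes no sample size

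*Protocol article*

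**What the plan says.** All statements are in the protocol article.

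- **GP outcome** (Sample size): "A sample of 14 GPs for each group will achieve 91.11% power to detect a mean difference in ACP self-efficacy of 1". The assumed SD is 0.71 per group and the test level 2.5%.
- **Patient outcome** (Sample size): "a sample of 26 patients for each group (corresponding to 13 GPs with each 2 patients") is given 91.45% power for a mean difference of 1 in the change score at the 2.5% level, "assuming the standard deviation is 0.96 in both groups". For the clustering, "we assume an intracluster correlation coefficient (ICC) of 0.04 [32], then the design effect is estimated at 1.04".
- **Sidedness** (Data analysis): "The analyses of the two separate primary endpoints will be performed at the two-sided 2.5% significance level".
- **Adopted size** (Sample size): each calculation is inflated for drop-out, to 17 GPs with 51 patients per group for the patient outcome and to 18 GPs per group for the GP outcome. The larger is adopted: 18 GPs and 54 patients per group.

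The section names no formula or software and states no target power.

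**The concern.** Each statement gives a group size, a difference, an SD, a significance level and a power to two decimals, so the power should follow from the rest. With a standard two-sample t-test calculation it does not, for either primary outcome, and both printed figures err in the favourable direction.

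For the patient outcome there is also the question of degrees of freedom. GPs are randomised, and the calculation rests on 13 of them per group. A design effect inflates the variance for clustering, but it does not reduce the degrees of freedom to the number of randomised units. With so few clusters this is visible in the result.

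At stake is whether a reader can reproduce the printed powers and take them at face value.

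**Working it through.** **Inputs.** From Sample size: difference 1; 14 GPs per group with SD 0.71; 26 patients per group with SD 0.96; ICC 0.04; cluster size 2. From Data analysis: two-sided 2.5%, so the critical value is the 0.9875 quantile.

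**Formulas.** Noncentrality: ncp = (difference / SD) × √(n/2), with n per group. Design effect: 1 + (2 − 1) × 0.04 = 1.04, so effective n for patients is 26/1.04 = 25. Exact power is the probability that a noncentral t variable with this ncp exceeds the t critical value in absolute size. The shortcut is Φ(ncp − t critical), which takes a t critical value but treats the statistic as normal.

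**Reproducing the printed figures.**

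- GP: ncp = (1/0.71) × √7 = 3.7264; df = 2 × 14 − 2 = 26; t critical = 2.3788. Φ(3.7264 − 2.3788) = Φ(1.3476) = 91.11%, as printed.
- Patient: ncp = (1/0.96) × √12.5 = 3.6829; df = 2 × 25 − 2 = 48; t critical = 2.3139. Φ(3.6829 − 2.3139) = Φ(1.3690) = 91.45%, as printed.

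A fully normal calculation gives 93.12% and 92.53%, so it is not the source.

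**Exact power with the same inputs.**

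| Outcome, per group | df | Printed | Shortcut | Noncentral t |
|---|---|---|---|---|
| 14 GPs | 26 | 91.11% | 91.11% | 90.35% |
| 26 patients, patient-level df | 48 | 91.45% | 91.45% | 91.05% |
| 26 patients, GP-level df (2 × 13 − 2) | 24 | 91.45% | 90.18% | 89.34% |

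Simulation with 400,000 replicates gives 90.4% for the GP t-test and 89.3% for a t-test on the 13 cluster means per group.

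**Differences.** GP: 91.11 − 90.35 = 0.76 points. Patient, like for like: 91.45 − 91.05 = 0.40 points. Patient, GP-level df: 91.45 − 89.34 = 2.11 points. Of that last gap, 91.45 − 90.18 = 1.27 points come from the change in df and 90.18 − 89.34 = 0.84 from the shortcut.

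**Could a rounded SD explain it?** No. An SD between 0.705 and 0.715 gives exact GP power of 90.8% down to 89.9%, never 91.11%. An SD between 0.955 and 0.965 gives exact patient power on 48 df of 91.35% down to 90.7%, never 91.45%.

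**Power at the adopted size after the plan's own drop-out.** 18 GPs less 22.22% leaves 14; 3 patients less 33.33% leaves 2; so 28 patients per group. Effective n = 28/1.04 = 26.92; ncp = (1/0.96) × √13.46 = 3.822. On GP-level df (2 × 14 − 2 = 26), exact patient power is 91.8%. GP power at 14 per group is the 90.35% above; if all 18 GPs stayed it would be 96.6%.

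**The case against.** The strongest reply is that nothing in the trial depends on this. The like-for-like differences are under one point, both corrected values stay above 90%, and no target power is stated that could be missed. Rounding of the GP SD alone moves power by about 0.9 points, more than the 0.76-point correction. All of this stands, and it is why the point is minor.

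A second reply is that the cause is inferred and that a t critical value with a normal tail is a recognisable approximation. That also stands. Two matches to two decimals are strong evidence, but not a statement by the authors. The discrepancy itself does not depend on the cause: the printed values are not the t-test powers for the stated inputs.

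A third reply is that keeping patient-level degrees of freedom after applying a design effect is a planning convention, and that the planned analysis is a linear mixed model on repeated measurements, not a t-test on cluster means. This is fair. The article does not fix the degrees of freedom of that model, so 89.3% is the value under GP-level counting and not the only defensible one. It is also mainly a cluster-counting matter, separate from the shortcut.

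A reader might infer that the planned sizes fail to deliver the stated power, or that the patient primary drops below 90%. The documents do not support either for the patient outcome. The 89.3% belongs to 13 GPs per group, what remains of 17, whereas the article adopts 18. At that size, after the assumed drop-out, patient power on GP-level degrees of freedom is 91.8%, above the printed 91.45%.

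**Conclusion.** The point holds as a small reporting correction. At the sizes they are attached to, the printed powers are too high by 0.76 points (GP: 90.3%, not 91.11%) and 0.40 points (patient: 91.1%, not 91.45%). If degrees of freedom are counted by GP, patient power at 13 GPs with 2 patients each is 89.3%.

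These values assume a two-sample t-test at two-sided 2.5%, normal outcomes, equal group sizes, and the article's SDs, ICC and design effect. For the GP outcome the correction also applies at the adopted size, because 18 GPs fall to the same 14 under the assumed drop-out. The patient outcome keeps at least its stated power there. The sample size and the significance level are not called into question.

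**What to change.** In the Sample size section:

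- Restate GP power at 14 per group as about 90.3%.
- For patients, either restate power at 13 GPs with 2 patients each as 91.1% (89.3% on GP-level degrees of freedom), or quote it at the adopted size after drop-out, 14 GPs with 2 patients each per group, as about 91.8% on 26 GP-level degrees of freedom. The second is preferable because it describes the trial being run.
- Add a phrase naming the method (noncentral t) and the degrees of freedom used.

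The cost is two figures and one phrase. Recruitment and the analysis are unchanged.

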### Recruitment

#### GPs

The research team will recruit GPs through several channels. Quality peer-review groups will be contacted to provide information about the study and motivate participation to their members. Publicly-available member lists of local associations of GPs and contact lists of GPs will be used for telephone and email contact and for providing recruitment letters by postal mail.

GPs who are eligible and wish to participate will be asked to provide informed consent. Each GP will be asked to list, with the help of a research assistant (RA), three patients who are potentially eligible for participation in the study. Where possible, each of the three identified patients should have a different life-limiting illness (cancer, organ failure, geriatric frailty) according to the criteria listed in Table 1.

#### Patients

GPs will have approximately 1 month to present the study to their selected eligible patients and ask them if they wish to participate. A simplified information letter will be provided to help explain the study. If the patient does not wish to participate, the GP will be asked to identify another potentially eligible patient within the same category of life-limiting illness. Eligible patients who agree to participate will be contacted via telephone by the research team, who will provide information about the study during a visit at the patient’s home or other location that is convenient for the patient, or via telephone if COVID-19 safety concerns prohibit face-to-face contact.

If a GP drops out during the first 3 months of the trial, a new GP will be recruited through the channels described below and trained to use the intervention. Reasons for drop-out will be discussed, recorded and taken into account for the process evaluation. If a GP withdraws from the study or drops out after 3 months, no new GP will be recruited. As only 3 patients will be enrolled per GP and the sample size has been increased to allow for a 23.53% GP drop-out and 33.33% patient drop-out, the drop-out of any one practice will not greatly impact the study.

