#### Control: care as usual

The intervention will be compared to a control group, which is care as usual. In this group, participating GPs will not receive the training or the conversation guides, and patients will not receive the workbook developed for the intervention. The control group will also not feature the two planned consultations dedicated specifically to discussing ACP as included in the intervention arm. Participating patients will consult with their GP as they usually do. During these consultations, the topic of ACP may still spontaneously be addressed, either by the GP or patient. Other already-available national documents, such as advance directive forms or patient guide materials, may be used as the GP or patients see fit.

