### Assignment of interventions

#### Allocation

Randomization will be performed at the level of the GP to avoid contamination bias. Every GP will have to recruit at least three patients. Once three patients have been recruited, the GP will be randomized to either the intervention or control group according to a 1:1 allocation ratio per a computer-generated randomization list. We will use permuted block randomization with varying block sizes. No stratification factors will be taken into account.

Participants will be enrolled to the study by the research assistants and data managers. The allocation sequence will be generated by independent statisticians working with the Biostatistics Unit at the Faculty of Medicine and Health Sciences of Ghent University. Assignment to intervention or control groups of GP-patient clusters will be performed by a researcher not involved with any other portion of this study.

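### The rule for replacing a GP lost in the first 3 months sends the new GP to intervention training with no stated randomisation step, which conflicts with the 1:1 allocation rule and the intent-to-treat set

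*Protocol article*

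**What the plan says.** The replacement rule is in the protocol article under Recruitment, Patients. The trigger is "If a GP drops out during the first 3 months of the trial", and the consequence is that "a new GP will be recruited through the channels described below and trained to use the intervention". For later losses the rule is the opposite: "If a GP withdraws from the study or drops out after 3 months, no new GP will be recruited".

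The allocation rule is under Assignment of interventions, Allocation: "the GP will be randomized to either the intervention or control group according to a 1:1 allocation ratio per a computer-generated randomization list", and this happens once three patients have been recruited. The Blinding section adds that consent and T0 data collection come before randomisation.

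The section on the control arm states that "participating GPs will not receive the training or the conversation guides"; control GPs are offered the training only after the study ends (Table 2).

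The Data analysis section defines the main population: "The intent-to-treat population consists of all patients randomized".

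The Sample size section already allows for GP loss: "This number has been increased to 18 GPs per group to allow for an initial GP drop-out rate of 22.22" per cent.

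**The concern.** During the trial, being trained is what distinguishes an intervention GP from a control GP. A rule that trains the new GP without condition therefore settles the arm at recruitment. Such a GP cannot also have an even chance of control from the randomisation list.

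Three protections would be lost for such a cluster. The GP would agree to take part knowing that training follows. The GP would select three patients knowing that they will receive the intervention. T0 would be answered with the arm known. The Discussion already accepts that GPs may pick patients with whom they are comfortable discussing advance care planning. When selection precedes allocation, that affects both arms alike; when it follows a known arm, it affects one arm only. Both primary outcomes are self-reported by participants who cannot be blinded, and the planned model has no term that separates non-randomised clusters from randomised ones.

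The intent-to-treat definition does not settle the matter. It does not say where a replacement GP's patients belong or what becomes of the cluster whose GP left. It also names only patients, although GPs are the randomised unit and carry one of the two primary outcomes.

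**Working it through.** **1. The plan's own figures.** Inputs from the Sample size section, with the two-sided 2.5% level from Data analysis:

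- GP level: 14 GPs per group, difference 1, SD 0.71. A two-sample t-test gives 90.3% power and the normal approximation 93.1%; the stated 91.11% lies between them.
- GP inflation: 1 - 14/18 = 22.22%, as stated.
- Patient level: 26 patients per group, design effect 1 + (2 - 1) x 0.04 = 1.04, effective size 26/1.04 = 25, difference 1, SD 0.96. The t-test gives 91.1% against the stated 91.45%.
- GP inflation in the patient calculation: 1 - 13/17 = 23.53%, as stated.

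The figures reproduce closely enough for the present purpose.

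**2. Is replacement needed for power?** Take the planned loss with no replacement:

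- GPs left per group: 18 x (1 - 0.2222) = 14, the number powered for (about 90%).
- Patients left per group: 14 x 3 x (1 - 0.3333) = 28, against 26 required.

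The inflation covers the loss that the replacement rule is meant to repair.

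**3. The rules side by side.**

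| Question | Allocation, Blinding and control sections | Replacement rule |
|---|---|---|
| When is the arm settled? | After three patients are recruited and T0 is done | Not stated; training follows recruitment |
| Chance of control | 1 in 2 | None, if training is certain |
| Who is trained during the trial? | Intervention GPs only | The new GP, whichever arm lost a GP |
| Place in intent-to-treat | All patients randomised | Not stated |

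The two columns cannot both apply to the same GP.

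**4. How many clusters could be affected?** Let a and c be the numbers of randomised GPs lost early in the intervention and control arms.

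- If only intervention losses are replaced, the non-randomised share of that arm is a/18.
- If every loss is replaced by a trained GP, which is the literal text, the share is (a + c)/(18 + c).

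| Early losses | Only intervention GPs replaced | Every loss replaced by a trained GP |
|---|---|---|
| none | 0 | 0 |
| 1 per arm | 1/18 = 5.6% | 2/19 = 10.5% |
| 4 per arm (the full 22.22%) | 4/18 = 22.2% | 8/22 = 36.4%, with 14 control GPs left |

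At three patients per GP, 4 of 18 GPs corresponds to 12 of 54 patients.

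**5. What would this do to the estimate?** The primary analysis takes the effect from the time x group interaction with T0 in the model. With complete data, a stable difference in level between replacement and randomised clusters is present at both T0 and T1 and cancels. What remains is

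bias = (non-randomised share) x (difference in T0-to-T1 change between replacement and randomised clusters that selection causes).

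The document gives nothing on the second factor, so the product cannot be computed.

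**The case against.** The strongest defence is that the replacement sentence is loosely worded and was never meant as an exception. The Allocation section speaks of every GP and exempts no one. The new GP comes through the study's recruitment channels, so the ordinary route is a natural reading. The sentence is also oddly placed: it sits under patient recruitment and points to channels below, although the GP channels are described before it. The window, near the start of the trial and close to the one-month period for approaching patients, may partly concern GPs who leave before randomisation, and replacing those is harmless. The article condenses a fuller protocol.

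Much of this stands, and it limits what can be claimed. It does not remove the conflict, because the article does state a rule and that rule makes training unconditional.

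A reader might go further in three ways that the document does not support:

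- That replacements are certain to bypass randomisation. The text omits the step; it does not say that the step is skipped.
- That drop-out will be heavier in the intervention arm because of the training and the conversations. This is plausible, but no arm-specific rate is given, and the sample size uses the same rate in both groups.
- That the bias can be found by multiplying 4/18 by a guessed difference in score level. A range of 0.25 to 0.75 points would give 0.06 to 0.17, but the range has no source, and a difference in level cancels from the time x group effect. Only a difference in change would remain.

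**Conclusion.** The point holds as a conflict within the protocol that needs to be resolved. As written, the rule for early replacement trains the new GP without condition. It cannot be reconciled with 1:1 list allocation after three patients and T0, with an untrained control arm, or with an intent-to-treat set of randomised participants. Followed to the letter, it would put non-randomised clusters in the intervention arm for both primary outcomes, and no analysis could restore their randomisation.

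The size is conditional. It is zero if no randomised GP leaves early. It reaches 4 of 18 GPs and 12 of 54 patients if the full 22.22% allowance is used, all of it early and after randomisation, and only intervention GPs are replaced. The literal reading, in which losses in both arms are replaced by trained GPs, gives 8 of 22. The 22.22% is a planning allowance, not a forecast. The direction and size of any bias in the primary effect cannot be determined from the document.

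**What to change.** Choose one of two rules and state it in both the Recruitment and the Allocation sections:

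- No GP is replaced after randomisation. The increase from 14 to 18 GPs per group already covers the planned loss.
- Or any additional GP enters as a new cluster: recruits three patients, completes T0 with them, and then takes the next allocation on the list, whichever arm that is. Training follows only if the allocation is to the intervention.

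Under either rule, a GP who leaves before randomisation may be replaced freely; say so, and say whether the 3-month window runs from the start of the trial or from the GP's own entry.

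In the Data analysis section, define intent-to-treat as all randomised GPs and their enrolled patients, analysed as allocated. Keep the cluster of a GP who leaves in the analysis under its allocated arm. A cluster that was never randomised does not belong in this set.

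The cost is wording only. The sample size and the models stay as they are.
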